**Figure 1 Fig1:**
[figure not shown]
Study flow of assessments and treatment for the attention-deficit hyperactivity disorder (ADHD) groups (in white) and the control group (in gray).

### Participants and recruitment

Participants of the ADHD group, as well as the healthy control group, are being recruited from the University of Tübingen student population, and non-student adults are being recruited through university mailing lists and by flyer. We are including all occupations and academic levels to have a diverse sample. The initial screening is conducted via phone and questionnaires are being mailed to check for the inclusion criteria. With the mailed questionnaires, potential participants also receive detailed information material and the informed consent form. The ADHD diagnostic assessment is scheduled if inclusion criteria are met. The control participants are being selected for age and sex and are included after the IQ test reveals them as a match for a patient.

### Ethics and written consent

This study (DRKS00006767) was approved by the local Ethics Committee (Ethics Committee for the Medical Department, University of Tübingen, Germany, Ethics votum number: 434/2010B01; Date 15 October 2012) according to the Declaration of Helsinki. Before entering the study, participants are informed about the study objectives, study design, and potential risks by one of the main investigators and are given this information in writing. Written consent is obtained from all participants.

Study-related information and informed consent is administered by the investigator(s) to ensure that participant questions and concerns are addressed. Participants receive the following information designed to educate him/her extensively on the subject of the investigation: information regarding the overall study; information on the goals, methods, and procedures of the study; and the end of the study plan. Participants are informed that they have the right to discontinue their participation at any time without giving a specific reason and without penalty.

### Inclusion and exclusion criteria

Participants include adults 18 years and older who meet the following inclusion criteria (please see “Assessments” section below for an explanation of all abbreviations):Attention Deficit Disorder inattentive type or hyperactive type or combined type according to DSM-IV criteria (ADHS-SB ≥18; WURS-K ≥30; WRI = adult ADHD).No additional serious physical, neurological, or psychiatric disorders with the exception of moderate depression (BDI-II score <28) and personality disorders, however, antisocial (SCID-II) or borderline personality disorders (BSL-23 ≤ 47) were excluded.Full scale IQ >80. 

Participants are excluded based on the following:Self-reported diagnosis of the following current symptoms: Serious physical illness or chronic diseases such as lung disease, heart disease, diabetes, hypertension, and rheumatic diseases; neurological disorders including Parkinson’s disease, stroke, multiple sclerosis and epilepsy; or indicated psychiatric disorders including bipolar disorder, psychosis, obsessive-compulsive disorder, chronic tics, Tourette syndrome, and suicidal behavior.Previous participation in another neurofeedback study.

The initial screening is conducted via phone and questionnaires are mailed to check for the inclusion criteria. The ADHD diagnostic assessment (see Table 1) will be scheduled if inclusion criteria are met. If the participants are on medications such as any short-acting stimulants, they are asked not to take them for at least 24 h prior to each assessment. For the neurofeedback treatment period, they may take their medication but on a stable dose. We do not stratify randomization for medication as we expect the usage to be very diverse.

**Table 1 Tab1:** **List of all assessments and their respective time of acquisition**

**Visit**	**Screening**	**Pre-test**	**Treatment phase 1**	**In between test**	**Treatment phase 2**	**Post-test**	**FU test**	**FU treatment**
**Assessment**								
ADHD-SB	X			X		X	X	
BDI-II	X			X		X	X	
BSL-23	X			X		X	X	
STAI	X			X		X	X	
CFT-20-R	X					X		
d2-R	X					X		
WRI	X					X	X	
SCID	X							
FERT			X		X			X
Checklist			X		X			X
WURS-K	X							
Sleep Q		X		X		X	X	
PANAS EHI	X	X		X		X	X	
PPI	X							
FEA-FFB	X							
FEA-AFB	X			X		X	X	
Medical Q	X							
EEG		X		X		X	X	
NIRS		X		X		X	X	

ADHD-SB, ADHS-Selbstbeurteilungsskala (German ADHD self-rating scale); BDI-II, Beck’s Depression Inventory; BSL-23, Borderline Symptom List; STAI, State Trait Anxiety Inventory; CFT-20-R, Culture Fair Test-20 Revised; d2-R, Test of Attention; FEA-FFB and FEA-AFB, Fragebogen zur Erfassung von ADHS im Erwachsenenalter, frühere/aktuelle Probleme - Fremdbeurteilung (German ADHD third-party rating scale); FERT, Fragebogen zur Erfassung relevanter Therapiebedingungen (German therapy effect rating scale); FU, Follw-up; SCID, Structured Clinical Interview for DSM-IV Disorders; WRI, Wender-Reimherr Interview; WURS-K, Wender Utah Rating Scale; PANAS, Positive Affect Negative Affect Schedule; EHI, Edinburgh Handedness Inventory; PPI, Psychopathic Personality Inventory; Q, questionnaire; EEG, electroencephalography; NIRS, near-infrared spectroscopy.

### Interventions

#### Slow cortical potential feedback

SCP feedback is conducted with the THERAPRAX (neuroConn GmbH, Ilmenau, Germany). The feedback protocol was developed by researchers at the Institute for Medical Psychology and Behavioral Neurobiology and has been used for many years in a variety of studies [56]. SCP are recorded at Cz referenced against mastoid A1 with a ground electrode on mastoid A2. Each SCP session consists of four runs of 40 trials, with each trial lasting 8 s and consisting of three phases: a baseline phase (seconds 0 to 2), an active phase (seconds 2 to 10), and a reinforcement phase (seconds 10 to 12) (See Figure 2). At the end of the baseline phase, participants are cued by a triangle directed to the top of the screen to “activate” their brain and by a triangle directed to the bottom of the screen to “deactivate” their brain. “Activation” in the SCP group means to produce an SCP shift in the electrically negative direction. “Deactivation” means to produce an SCP shift in the electrically positive direction. In all sessions, trials with required activation and deactivation will be randomly distributed and make up 50% of all trials.

**Figure 2 Fig2:**
[figure not shown]
Neurofeedback trial set-up: 2sec baseline, 8sec active phase and 2sec reinforcement phase.

Participants are trained one to three times per week (maximum of five times per week) for a total of 30 sessions. Each session lasts about an hour, including the preparation time and is divided into four 8-min blocks. To generalize newly acquired regulation skills to everyday life situations, the third block in each session serves as “transfer block” in which no visual feedback is presented during the active feedback phase of each trial. The level of success is indicated with the visual reward system only. Participants are instructed to use their self-regulation in everyday life situations. After the 15th session, participants are provided with a 15 × 5 inch picture of the neurofeedback screen as a memory aid as well as a CD playing a video of the transfer trials without feedback to help the transfer to daily life.

#### Near-infrared spectroscopy feedback

The extent of prefrontal activation in terms of changes in O_2_Hb concentration is displayed online on a computer screen. Based on previous fMRI feedback protocols and the SCP-feedback screen described above, participants are instructed via visual commands (triangle on the screen) to regulate PFC activity up (“activation period”) or down (“deactivation period”). During the activation period, upregulation of PFC activity is operationalized as an increase in the concentration of O_2_Hb within a predefined region of interest (NIRS channels covering left and right lateral prefrontal areas). During the deactivation period, on the other hand, participants should achieve a decrease in O_2_Hb concentration within the same target region. Functionally, such a decrease in prefrontal oxygenation below baseline levels will probably be associated with an increased blood supply in other parts of the brain, for example, visual association areas or parts of the default network. In between each “active” period (activation versus deactivation), rest trials ensure a return of hemodynamic activation to baseline levels. One session consists of a total of 24 activation periods (30 s each), separated by 30-s resting periods. Also in accordance with the SCP feedback protocol (see above), the ratio of “activation” to “deactivation periods” is 50/50 over the course of all sessions. Moreover, a block of eight “transfer trials” will be included after the first block of 12 activation trials. Participants will be trained one to three times per week for a total of 30 sessions. Each session lasts about 40 minutes, including preparation time.

#### Electromyogram feedback

For the EMG feedback, an EMG biofeedback application is used based on the protocol being already used in the above-mentioned clinical study “Neurofeedback in children with ADHD” (Ho 2503 4/1) [57]. EMG electrodes are placed over the right and left musculus supraspinatus. In addition, EEG electrodes are placed onto the scalp to imitate an EEG or NIRS recording. The relation between relaxation on the left and tension of the right muscle is used as the feedback signal when participants are asked to regulate the signal up. To regulate it down, the left muscle has to become tense while the right has to be relaxed. Trial length, visual output, transfer trials and overall duration resemble the SCP neurofeedback as described above as closely as possible.

Preliminary data from the multicenter controlled randomized study for children with ADHD [57] show superior outcome for SCP compared to EMG. In another pilot study, children with ADHD underwent NIRS feedback with comparable outcome after 12 sessions to SCP feedback [58]. This is the first study to investigate adults, and we use an identical design to rule out nonspecific effects. We compare two neurofeedback techniques (control of metabolic and electrophysiological parameters) in their effectiveness. In a second step we try to rule out nonspecific effects by using a placebo-controlled training (EMG). Expectancy effects are assessed with a questionnaire (FERT - see below) and will be included in the analysis.

### Control group

The healthy controls undergo only part of the diagnostic procedure, including the ADHD-SB, BDI, STAI, EHI, BSL, d2, CFT-20-R (see section below for explanation), demographic and medical history questionnaires, and the EEG and NIRS assessment. The controls are assessed at two time points but do not receive any treatment in between. The first measurement is being performed directly after the recruitment and screening procedure. The time between the first and the second measurement is dependent on the amount of time it takes the matched patient to complete treatment (+/− two months).

### Randomization and blinding

The randomization is conducted in two steps: first a blockwise randomization, and second a pairwise randomization for age, sex and IQ. We determined a grouping order (EEG = 1; NIRS = 2; and EMG = 3). If the participant does not fit into group 1, he/she is matched to group 2 and if not group 2, then group 3. For the next participant, the matching process starts in group 2 and so forth.

The participants are not blinded to the treatment condition, as it is easier to achieve physiological self-control knowing which parameter has to be controlled. Further, blinding was not possible, due to the different feedback methods that made it obvious which treatment was being applied and received (for example, NIRS vs. EEG measurement setup). The different methods are used in different labs and with different technical requirements, and therefore, neither blinding of participants nor blinding of assessors was possible.

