## Methods/Design

In this proof-of-principle study, a total of 60 adult participants diagnosed with ADHD (combined, hyperactive, or inattentive type) are randomly blockwise assigned to SCP, NIRS, or electromyogram (EMG) feedback groups (n = 20 each) stratified for age, sex, and educational level. This is the first study to investigate and compare the efficacy of these treatment modalities in an adult ADHD population.

Twenty healthy controls matched for age, sex, IQ, and pre- and post-treatment duration will be included in the neurophysiological assessments for pre- and post-treatment measurement in order to establish “expected” activation patterns and allow for a more thorough interpretation of changes following the neurofeedback treatment. The study objectives are as follows:Assess whether there are physiological differences (EEG and ERP) in ADHD participants compared to healthy controls.Assess whether adult participants are able to demonstrate learning of cortical self-regulation.Assess whether treatment leads to an improvement in cognition (that is, attention and working memory) and behavior (that is, restlessness and impulsivity), and changes in specific EEG or NIRS parameters.Assess whether specific methods and protocols are more efficacious in changing behavioral, cognitive, and EEG and NIRS outcome variables.Assess whether changes are stable at the 6-month follow-up.Assess whether specific methods and protocols differ in the stability of cortical self-regulation and clinical effects at the 6-month follow-up.Assess whether the efficiency of the different training protocols differs depending on individual neurocognitive baseline parameters (for example, frontal lobe activation during neuropsychological assessments; baseline CNV etc.).

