## Discussion

This paper presents the protocol and design of a randomized controlled trial with two types of neurofeedback (SCP and NIRS) and an active control (EMG biofeedback) condition for adults with ADHD. This is the first study to systematically investigate neurofeedback in adults with ADHD. It is also the first study to compare SCP and NIRS feedback to an active control condition on the one hand and to investigate this in an adult ADHD population on the other hand.

If one or both feedback types are superior to the control condition, a first step will be made towards a new acknowledged treatment option for adult ADHD.

This is not the “gold standard” design for treatment studies, which is a placebo-controlled randomized double blind design [76]. The problems with this approach are widely discussed elsewhere [77,78]. Therefore, to allow for all therapeutic aspects of neurofeedback therapy to come into effect, such as a good patient-therapist relationship, psychoeducation, and strengthening of self-efficacy expectations, we decided to use an active control condition that was used in other studies before. The study design was based on a study protocol of a multicenter treatment study with ADHD children [57]. The use of EMG feedback as an active control condition is based on the rationale that EMG feedback is not an “empty” treatment, but will induce identical nonspecific (placebo) effects that will help to differentiate between specific effects of the neurofeedback and nonspecific effects from the above-mentioned aspects.

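### The only allocation rule the article describes is a deterministic, rotating 'fit or next group' cascade, which cannot be reconciled with the randomisation it claims

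*Protocol article*

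**What the plan says.** Three places in the protocol article describe the allocation.

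- **Methods/Design**: 60 adults are assigned at random in blocks to SCP, NIRS or EMG feedback, 20 per group, "stratified for age, sex, and educational level".
- **Randomization and blinding**: "The randomization is conducted in two steps: first a blockwise randomization, and second a pairwise randomization for age, sex and IQ". The groups are then numbered in a set order (EEG, meaning SCP, is 1; NIRS is 2; EMG is 3), and the working rule follows: "If the participant does not fit into group 1, he/she is matched to group 2 and if not group 2, then group 3". The starting point then moves on: "For the next participant, the matching process starts in group 2 and so forth".
- **Discussion**: the paper presents "the protocol and design of a randomized controlled trial".

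The Randomization and blinding section also states that "neither blinding of participants nor blinding of assessors was possible". It does not say who applies the rule, whether recruiting staff can see the next starting group, what makes a participant fit a group, or how the blockwise step feeds into the cascade.

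**The concern.** Random allocation needs a step whose result cannot be worked out beforehand. The rule described has a fixed order, a fixed rotation and a fixed fallback. Someone who knows the entry position knows which group is tried first. Someone who also knows the participant's covariates and the current groups can work out the assignment, to the extent that fit has a definite meaning. Where it has none, discretion fills the gap.

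At stake are the SCP–EMG and NIRS–EMG comparisons. The Discussion would read superiority over EMG as a first step towards an acknowledged treatment, and that reading needs groups that differ at entry only by chance. With 20 per group, a modest prognostic difference matters. The planned tests also take their error rates from random assignment.

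**Working it through.** **1. The plan's own figure.** From Sample-size calculation: effect size 0.81, one-sided α 0.05, power at least 80%. The normal approximation gives n = 2 × (1.645 + 0.842)² / 0.81² = 18.8, so 19 per group. The two-sample t-test gives 19.56, so 20, with power 0.808. The stated 20 per group is reproduced and is not in question.

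**2. Where chance enters the described rule.**

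| Element | As described | Chance step? |
|---|---|---|
| Group order | fixed 1, 2, 3 | no |
| Starting group | moves on by one per participant | no |
| If no fit | go to the next group in order | no |
| Fit | undefined match on age, sex and IQ | none stated |

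The labels blockwise and pairwise randomisation have no counterpart in these steps. A random block list and a rotation that itself fixes the group cannot both decide the assignment; one must override the other, and the text does not say which.

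**3. Predictability.** Assume a participant fits any given group with probability f, independently, and that the last group is forced. The final group is then the starting group with probability f, the second with f(1 − f) and the third with (1 − f)². The article gives no value for f.

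| f | Starting group | Second | Third |
|---|---|---|---|
| 1.00 | 1.00 | 0 | 0 |
| 0.90 | 0.90 | 0.09 | 0.01 |
| 0.75 | 0.75 | 0.19 | 0.06 |
| 0.50 | 0.50 | 0.25 | 0.25 |

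For comparison, a guess is right 1/3 of the time under simple 1:1:1 randomisation. Under permuted blocks of 3 with full knowledge of the history it is right (1/3 + 1/2 + 1)/3 = 0.61 of the time; for blocks of 6 and 9, simulation gives 0.56 and 0.53. Those higher rates are the fairer comparator, since the article names blocks. A person who knows only the starting group does better than this if f exceeds about 0.6. A person who also knows the covariates and the groups can derive the assignment whatever f is.

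**4. Illustration of consequence (assumed steering, no true effect).** Suppose entrants whose starting group is SCP have expected outcomes s SD better than those whose starting group is EMG. Misdirected participants dilute this, and the expected SCP–EMG bias is [f − (1 − f)/2] × s = (3f − 1)/2 × s. For f = 0.75 and s = 0.2 this is 0.625 × 0.2 = 0.125 SD. The rejection rate of a one-sided t-test (20 per arm, 38 df, critical value 1.686) uses noncentrality bias × √10.

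| f | s | Bias (SD) | Type I error |
|---|---|---|---|
| 0.75 | 0.2 | 0.125 | 10.4% |
| 1.00 | 0.2 | 0.200 | 15.3% |
| 0.75 | 0.5 | 0.313 | 25.0% |
| 1.00 | 0.5 | 0.500 | 46.3% |

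A simulation of the steering with 60 participants gives 10%, 16%, 24% and 46%. Neither f nor s is in the article.

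**5. Balancing factors.** Methods/Design lists age, sex and educational level. Randomization and blinding has "second a pairwise randomization for age, sex and IQ". Age and sex agree; the third factor does not.

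**The case against.** The strongest reply is that the article does claim a random step. It puts a blockwise randomisation first, and Methods/Design speaks of random blockwise assignment. A condensed article may leave block sizes, sequence handling and concealment to the full protocol, so their absence proves nothing. This stands in part. A reader might infer that staff ran the allocation in the open, judged fit by discretion and that the trial was not randomised at all. The documents do not support that: they do not say who applies the rule or whether it is concealed, and unblinded participants and assessors are not the same as unconcealed allocation. The reply does not remove the finding, because the article did not leave the mechanism out. It described one, and that mechanism has no chance step.

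The error rates in the illustration come from an assumed prognostic shift, and any bias of the same size from another source would produce them. They also come from a single two-arm t-test, while the Statistical analysis section plans a three-group by four-assessment ANOVA. Both points are right, so the figures show scale only. It is also right that knowing the starting group is not knowing the final group.

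Educational level and IQ might belong to different steps, blockwise and pairwise. The text permits this but does not say so, and the two descriptions still need to be reconciled.

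**Conclusion.** The point holds as a contradiction and a risk. The label is randomised, the described rule is deterministic, and nothing in the article reconciles them. That the rule as written contains no chance step follows from the text alone and needs no assumption. The size of any bias does need assumptions: for f between 0.75 and 1 and a prognostic shift of 0.2 SD, one-sided type I error is about 10% to 15% against a nominal 5%; without steering there is no such inflation.

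Two stronger readings go too far. That selection bias occurred is not shown. That no participant was randomised is not shown either, because the blockwise step may have operated in a way the article does not explain. The sample size is unaffected. The matter should still be settled before results are reported, because the comparison with EMG rests on it.

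**What to change.** The Trial status section says the trial is ongoing, so the change can still be made for participants not yet allocated.

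1. Replace the cascade with a computer-generated allocation that has a random element. One suitable form is minimisation on age, sex and one agreed third factor (IQ or educational level, named identically in both sections), with the best-balancing arm chosen with probability below 1.
2. Release each assignment only after eligibility is confirmed, and conceal upcoming assignments from recruiting staff.
3. Adjust the analysis for the allocation factors.
4. For those already enrolled, report how each was allocated, what counted as a fit, how the blockwise step worked and where chance entered, if it did. Give the numbers under each method and a sensitivity analysis by allocation method.
5. Do not call the allocation randomised for any participant assigned by the deterministic cascade alone.

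The cost is a short amendment and slightly looser covariate balance than direct matching. No extra participants or visits are needed.

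### The allocation rule as described is a rotating fixed order with matching and shows no chance element, which conflicts with the trial's description as randomised

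*Protocol article*

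**What the plan says.** The Methods/Design section of the protocol article says that 60 adults are "randomly blockwise assigned to SCP, NIRS, or electromyogram (EMG) feedback groups (n = 20 each) stratified for age, sex, and educational level". The Discussion opens with "This paper presents the protocol and design of a randomized controlled trial with two types of neurofeedback".

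The section on randomization and blinding gives the procedure in four sentences:

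- The label: "The randomization is conducted in two steps: first a blockwise randomization, and second a pairwise randomization for age, sex and IQ".
- The order of arms, set by the investigators: "We determined a grouping order (EEG = 1; NIRS = 2; and EMG = 3". EEG here is the SCP arm.
- The pass-on rule: "If the participant does not fit into group 1, he/she is matched to group 2 and if not group 2, then group 3".
- The rotation: "For the next participant, the matching process starts in group 2 and so forth".

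No threshold for fit is given. The same section states that "neither blinding of participants nor blinding of assessors was possible".

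**The concern.** The label and the rule do not agree. Block randomisation needs a random order of arms within each block. The described rule has a fixed order, a starting arm that advances systematically, and a matching judgement. Nothing in it is left to chance.

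Predictable allocation matters because the arm can then influence who enters it. A candidate could be admitted, deferred or judged not to fit with the likely arm in view. Age, sex and IQ are all available from screening (the medical history questionnaire and the CFT-20-R), so fit can be judged before an arm is assigned.

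Two features of this trial raise the stakes. It is unblinded throughout. Its primary outcomes are a self-report scale (ADHS-SB), a third-party questionnaire (FEA-AFB) and an interview (WRI), all of which are open to expectation. Adjusting for measured baseline variables would not remove a difference in unmeasured traits, such as motivation to complete 30 sessions.

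**Working it through.** **1. Tracing the rule.** Inputs are the fixed order (EEG 1, NIRS 2, EMG 3), the pass-on rule and the rotation, all from the section on randomization and blinding.

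| Participant | Arm tried first | If no fit | Then |
|---|---|---|---|
| 1 | EEG | NIRS | EMG |
| 2 | NIRS | next in order | next in order |
| 3 | EMG (implied) | next in order | next in order |
| 4 | EEG (implied) | NIRS | EMG |

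The first-tried arms for participants 1 and 2 are stated; those for 3 and 4 follow from the rotation continuing. The assigned arm is therefore a function of arrival order, the participant's covariates, those already enrolled and the fit judgement. No term in that function is random.

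**2. Setting the sections side by side.**

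| Item | Methods/Design | Randomization and blinding |
|---|---|---|
| Mechanism | random, blockwise | two steps labelled randomisation; the rule given is a rotating fixed order |
| Balancing factors | age, sex, educational level | age, sex, IQ |

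The mechanism and the third balancing factor both differ.

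**3. Predictability.** Let q be the chance that a participant fits the first-tried arm.

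- Someone who knows only the rotation and guesses the starting arm is right with probability q. The article gives no q. If q is assumed to lie between 0.5 and 1.0, the rate is 50% to 100%.
- Someone who also knows the covariates, the current enrolment and how fit is judged can work out the arm every time.
- Benchmark for permuted blocks of 3, with past assignments and block size known: (1/3 + 1/2 + 1)/3 = 0.611.
- The same benchmark is 0.561 for blocks of 6, 0.532 for blocks of 9 and 0.512 for blocks of 12. Simple randomisation gives 0.333.

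**4. The plan's own figure.** The sample-size section uses an effect size of 0.81, one-sided alpha of 0.05 and at least 80% power. The noncentrality is 0.81 × √(20/2) = 2.56, with 38 degrees of freedom and a critical t of 1.686. Power is 80.8%, so 20 per group reproduces (19 by the normal approximation). The present point does not alter this figure.

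**5. Illustration of the consequence.** This uses the same one-sided t-test with 20 per arm and no true effect. The spurious prognostic difference d between two arms is assumed to favour the tested arm.

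- Noncentrality = d × √10
- d = 0.25: 0.79, rejection probability 19.3%
- d = 0.50: 1.58, rejection probability 46.3%

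The nominal rate is 5%. Both values of d are assumptions; nothing in the article supplies one.

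**The case against.** The strongest reply is that the section does assert a first step of blockwise randomisation. The fixed order and matching may describe only the second, pairwise step, and a journal article often leaves sequence generation and concealment to the full protocol. That stands in part. A reader might infer that no random draw was ever made and that the arms were not randomised. The document does not establish that; it shows only that no random step is visible in the rule it describes. But this is more than condensation. The article sets out a mechanism, that mechanism conflicts with its label, and the fixed order with a rotating start leaves no evident place for a random step.

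A reader might also infer that recruiting staff know the next arm and judge fit themselves. The article does not say who allocates, who judges fit or when the arm is revealed. Its remarks on blinding concern participants and assessors, not allocation concealment. Steering is therefore a possibility, not a reported fact. Only the starting arm is always known in advance. To say the arm is predictable with certainty holds for someone with only the rotation solely when the participant is already known to fit that arm, so it should not be set against the unconditional 0.33 or 0.61.

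Finally, the 19% to 46% range uses a two-arm t-test, whereas the plan is an ANOVA of three groups by four assessment points that includes the pre-treatment value. Steering on stable symptom level would largely cancel there; steering on expected change would not. The arithmetic is correct, but the range remains an illustration.

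**Conclusion.** The point holds as a defect in the described rule. The only allocation mechanism the protocol article describes is alternation with matching on an undefined criterion, and it contradicts the article's two statements that the trial is randomised. The balancing factors also contradict each other. If the rule is followed as written, allocation is predictable at its starting arm and open to steering at its final arm, and every SCP, NIRS and EMG contrast could be biased.

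Confidence is high on what the text says and lower on what was done in practice. The size of any bias cannot be derived from the document. The rise from 5% to about 19% to 46% rests wholly on an assumed shift of 0.25 to 0.5 SD favouring the tested arm. Because every between-arm claim depends on allocation and the trial is described as ongoing, this must be fixed.

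**What to change.** 1. Reconcile the balancing factors: the Methods/Design section names educational level, the randomization section IQ.
2. If a genuine random step exists, correct the randomization section to state it, define fit, and say how the sequence is concealed.
3. If none exists, allocate all remaining participants by a concealed computer procedure with a random element. Minimisation on the reconciled factors with a biased coin would serve. Reveal the arm only once eligibility and the pre-test are complete.
4. In that case, report participants already allocated by the rotation as quasi-randomised, and give their number.

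The cost is a short amendment and slightly looser balance on the matching factors; the planned sample size does not change. The article does not say how many participants have been allocated, so the benefit of changing the procedure depends on how many remain. An analysis by allocation method is not required, since with 20 per arm it could be uninformative.
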